### **6.10.1 Infection prevention control strategies questionnaire (IPC) (frequency: baseline and end of March)**

Staff will be asked to report their beliefs and confidence in IPC using 5-point Likert scales (strongly agree/ agree/ not sure/ disagree/ strongly disagree) in response to the following statements:

- Lack of time prevents me from always following infection prevention and control procedures.
- I am confident my use of infection prevention and control procedures is effective.
- I believe infections can be spread through the air, for example as droplets from a sneeze or cough.
- I believe air filters reduce infections being spread through the air.

### **6.10.2 Care home satisfaction questionnaire (frequency: baseline and end of March only)**

Staff will be asked to completed a care home satisfaction questionnaire using 5-point Likert scales (very satisfied/ satisfied agree/ not sure/ dissatisfied/ very dissatisfied) about their overall satisfaction with the care home environment (e.g. air temperature, odours).

### **6.10.3 Air filter satisfaction questionnaire (frequency: intervention care homes/end of March only)**

All care home managers and staff will be asked to report their satisfaction with air filters using 5-point Likert scales (very satisfied/ satisfied agree/ not sure/ dissatisfied/ very dissatisfied) for all air filters (staff rooms, communal rooms and private bedrooms).

## **6.11 Resident Questionnaires**

### **6.11.1 Infection Prevention Control Strategies Questionnaire (frequency: baseline and end of March)**

Residents will be asked to report their beliefs and confidence in IPC using 5-point Likert scales (strongly agree/ agree/ not sure/ disagree/ strongly disagree) in response to statement such as the following:

- I believe infections can be spread through the air, for example as droplets from a sneeze or cough.
- I believe air filters reduce infections being spread through the air.

### **6.11.2 Care Home Satisfaction Questionnaire (frequency: baseline and end of March)**

Residents/consultees will be asked to complete a care home resident satisfaction questionnaire using 5-point Likert scales (very satisfied/ satisfied agree/ not sure/ dissatisfied/ very dissatisfied) about their overall satisfaction with the care home environment (e.g. sleep quality, air temperature, odours). The approximate amount of time residents spend in communal areas will also be captured.

### **6.11.3 Air filter Satisfaction Questionnaire (frequency: intervention care homes/end of March only)**

Residents/consultees will be asked to complete a resident air filter satisfaction questionnaire about their overall satisfaction of the air filter in their bedroom using 5-point Likert scales (very satisfied/ satisfied agree/ not sure/ dissatisfied/ very dissatisfied).

## **6.12 UK Health Security Agency (formerly Public Health England) (collected retrospectively)**

UK Health Security Agency (UKHSA – formerly Public Health England) data regarding outbreaks within the care home will be collected in an anonymised format for the whole care home (this will include residents who opt out due to the anonymous format). This data is expected to include:

- SARS-CoV-2 PCR testing: this data is collected by the care home when a PCR test has been requested. The results of this test will also be known.
- Other respiratory virus testing: this data is also a requirement to be collected by the care home for cases of influenza A and B and other respiratory viruses.
- Other infections: This includes Streptococcal, Meningococcal, Respiratory Syncytial Virus, Norovirus and Human Metapneumovirus infection testing which will also be required by the care home to provide this data to UKHSA.
- With consent, the research team will share identifiable information about the “consented” (which may include initials, NHS number, full name, date of birth) with UK Health Security Agency (formerly Public Health England) so that they can provide the University of Bristol with relevant information about study outcome measures, for example infection outbreaks in the care home and mortality data.

## **6.13 New residents**

New residents joining the care home will be informed of the study and will be added to the anonymised resident registry. They may be added to the randomly selected pool of “the 30” residents for data collection / potentially invited to consent if any of “the 30” opt-out of the study. Where care homes have  $\leq 30$  residents, data collection will commence on new residents unless they opt out of study involvement, or they become a resident in the care home after the after 1 May, since they will not be able to contribute at least 1 month of data collection.

## **6.14 Qualitative outcomes**

See section 8.

## **6.15 Change in participation status of care homes and participants**

In all instances, data collected up to the date of the change/opt-out will be retained by the trial in accordance with GDPR regulations.

### **6.15.1 Care home change in participation status**

Any care home can request to change their participation status in the study at any time. The care home can change their participation by requesting to stop any of the following:

- i) Air filters in resident communal areas
- ii) Air filters in staff communal areas
- iii) Air filters in resident private bedrooms
- iv) Data collection for residents
- v) Data collection for staff
- vi) Complete discontinuation of all trial procedures. If this is decided, the care home will end all involvement in the trial, including activities associated with the individually consented residents. If a care home does wish to withdraw completely, they will be required to complete a study change in participation status form and will need to arrange return of the air filters (intervention homes only).

Note: If a care home changes their participation status, permission will be sought to continue with the GP notes review for individually consented participants).

### **6.15.2 Resident change in participation status**

Consented residents can request to change their participation status in the study at any time. They can change their participation by requesting to stop any of the following:

- i) Having an air filter in their private bedroom (intervention residents only)
- ii) Access to their medical records

Even if a resident decides to change their participation by no longer having an air filter in their bedroom or allowing access to their medical records, they can still contribute data to the daily anonymised data collection elements (unless they opt-out of this).

If a consented resident changes their participation in the study between the period 1st Sept to 1st May, a replacement resident will be sought following the procedures in sections in section 6.5; consent to join trial, baseline data collection and follow up. If a resident in the intervention group decides they no longer want an air filter in their private bedroom, the newly consented resident will be offered the same shell air filter unit but the study will supply a new inner air filter. Used air filters may be sent to the laboratory for storage as detailed in section 10.7.

### **6.15.3 Resident opt-out**

Throughout the set-up of the trial at the care home and during follow-up, if a resident (or a consultee) decide they do not want their data included in the trial, they can opt-out of the anonymised data collection at any time from their data being collected from baseline through to end of follow-up. This will be recorded on the trial resident register by the care home staff and if a reason for the opt out is given, this will be recorded.

## **6.16 Care home closedown**

### **6.16.1 Care home study paperwork, tablets and electricity monitors**

At the end of the winter period, care home managers will ensure all study paperwork is logged online and any hard-copies are returned via secure post to the University of Bristol. Similarly tablets, electricity monitors and extension cords will also be returned to Bristol.

### **6.16.2 Removal of air filters**

At the end of the care home data collection period, care home staff may be asked to remove the filters from the air filter unit. If this is the case, they will use the materials provided to label and package the filters and arrangements will be made to send the used filters to the research laboratory (see section 10.7).

The remaining 'shell' units will be offered to the care homes and residents for use with new filters that they would be responsible for purchasing. If, for any reason, the used filters are not required by the study team, appropriate arrangements will be made with the individual care homes for the used internal filters (e.g. local disposal according to manufacturer guidance).

### **6.16.3 Thanking care home staff for their involvement**

At the end of the care home data collection period, the study team will provide 'study certificates' for all care home managers and study champions.

### **6.16.4 Thanking residents for their involvement**

The study team will provide a large colour poster to hang on the communal room wall thanking the residents for their help with the study. In addition, the study team will provide consented residents with a thank you card.

The study team will contribute to an appropriate gift/vouchers as guided by the PAG group and care home managers.

## **6.17 Methods/procedures to protect against other sources of bias**

Randomisation will be at care home level stratified by nursing care provision and socioeconomic status, because infection transmission occurs within care homes between staff and residents, and we anticipate individual use of air filters could benefit non-users.

To minimise post-randomisation bias, the care home/care home staff will complete baseline care home data prior to randomisation. Where possible, staff questionnaires will also be completed before data collection starts.

Previous research suggests ~30% of residents will wish to take part and ~40% will leave the care home or die during the study,(34) reflecting the frailty and vulnerability of the study population. To maintain study power, we will continually recruit new residents, resulting in an expected overall study dropout ~20%. Sensitivity analyses will be used to investigate the potential impact of this strategy, including checking for evidence of post-randomisation recruitment bias.

Primary outcome attrition will be minimised through the use of short, simple-to-complete, staff administered symptom questions.

The process evaluation will assess if use of air filters results in any unintended relaxation of infection prevention and control procedures.

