| c. Working days lost to sickness due to any other infection                                                                                                                                                                                      | CH manager CRF/eCRF daily/weekly                                                      |
| d. Change over time in staff confidence in, and use of, infection prevention and control strategies.                                                                                                                                             | Staff questionnaires                                                                  |
|                                                                                                                                                                                                                                                  |                                                                                       |
|                                                                                                                                                                                                                                                  |                                                                                       |
|                                                                                                                                                                                                                                                  |                                                                                       |
| e. Perception of care home environment                                                                                                                                                                                                           | Staff questionnaire (optional)                                                        |
| Secondary objective 3 (Care Homes)                                                                                                                                                                                                        |                                                                                       |

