#### **6.4.4 Care home baseline data collection**

Baseline data collection will include data captured on the EoI form and the information detailed below. The care home manager will complete this using an online care home baseline data collection form. We understand some data will vary with time, and that this is essentially a baseline cross sectional survey.

Staff roles and numbers (FTE, permanent and agency); CQC rating; number and type of rooms in care home; care home ventilation policy (windows open/closed); IPC policy; care home manager and additional study champion contact details; funding (private/public); use of additional air filters in communal, staff and private bedrooms (acquired outside of the study).

For all eligible residents, regardless of consent status the following anonymised aggregate baseline data will be collected by trained staff: age; sex; ethnicity; receiving nursing care; vaccination status.

On an individual basis residents' frailty will also be assessed using the clinical frailty scale (a judgement-based frailty tool that evaluates specific domains including comorbidity, function, and cognition to generate a frailty score ranging from 1 (very fit) to 9 (terminally ill)).

Staff will be asked to complete the (optional) infection prevention and control & care home satisfaction questionnaires (see section 6.10).

We will also ask care homes to provide a copy of their local safeguarding policies for the study records.

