#### **6.4.5 Randomisation and allocation specific training**

Following green light activation, and baseline data being received, the care homes will be randomised to receive either the intervention (usual care plus HEPA filters) or control (usual care) (see section 10 and 11). Randomisation will be stratified by whether they provide nursing care yes/no; and socioeconomic tertile (high/medium/low)) using a randomisation list pre-generated by a CTU statistician with no other involvement in recruitment activities.

Following randomisation, care homes will be informed of their allocation.

Intervention care homes will complete additional study training, specific to the use of devices in their care homes – e.g. installation, monitoring and maintaining air filters (according to manufacturer instructions), recording of outcomes and the arrangements for delivery of the air filters to the relevant care homes. For care homes allocated to the intervention, training will also involve discussions of where to locate communal room air filters. Staff will then begin inviting an average of 12 (maximum of 16) residents per care home to participate to receive an air filter in their private bedrooms and/or provide access to their medical records (see section 6.5) and share identifiers with the UKHSA.

In the control care homes staff will begin inviting an average of 12 (maximum of 16) residents per care home to participate provide access to their medical records (see section 6.5) and share identifiers with the UKHSA.

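### The protocol lets the staff 'baseline' infection-control questionnaire be completed after the home knows its allocation, which may bias the change-over-time outcome (2d) by an unknown amount and in an unknown direction

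*Protocol*

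**What the plan says.** Three parts of the protocol bear on when staff complete the baseline questionnaires.

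- Section 6.4.4 lists them with the care home baseline data: "Staff will be asked to complete the (optional) infection prevention and control & care home satisfaction questionnaires". Section 6.4.5 then says "Following green light activation, and baseline data being received, the care homes will be randomised". Read together, these put the questionnaires before randomisation.
- Section 6.17, under the aim of limiting post-randomisation bias, separates the two. It says "the care home/care home staff will complete baseline care home data prior to randomisation", and the next sentence gives the questionnaires a later and softer limit, namely that, where possible, "staff questionnaires will also be completed before data collection starts".
- Section 6.4.5 also says "Following randomisation, care homes will be informed of their allocation". Section 6.19 confirms that site staff are not blinded.

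The outcome that depends on this baseline is staff secondary outcome 2d in Table 1 (Section 2.5), defined as "Change over time in staff confidence in, and use of, infection prevention and control strategies" and measured by staff questionnaire. Section 6.10.1 sets the measurement times as baseline and the end of March. Its items cover time pressure, confidence in one's own practice, airborne spread, and the statement "I believe air filters reduce infections being spread through the air".

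**The concern.** An outcome defined as change from baseline compares arms fairly only if the baseline could not have been influenced by the arm. Section 6.17 applies that principle to the care home data but not to the staff questionnaires. If staff answer after learning that their home will, or will not, receive filters, their starting scores may already differ by arm for that reason. Subtracting or adjusting for those scores then takes part of the allocation effect out of the comparison, or adds a spurious component to it. At stake is the interpretation of one secondary staff outcome. The staff perception-of-environment questionnaire is exposed in the same way if its analysis uses the same baseline.

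**Working it through.** **Order of events.** The protocol states no figure on this point, so the first check is the sequence.

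1. Green light, which depends on set-up documents including aggregate care home baseline data (6.4.2).
2. Randomisation once baseline data are received (6.4.5).
3. Home told its allocation (6.4.5).
4. Device-specific training in intervention homes (6.4.5).
5. Residents invited and consented (6.4.5, 6.5).
6. Data collection starts once enough residents, usually at least 7, have consented (6.7).
7. Filters switched on after two days of data collection (6.7, 10.4).

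Sections 6.4.4 and 6.4.5 place the staff questionnaires before step 2. Section 6.17 sets the limit at step 6, and only where possible. Steps 3 to 5 lie between the two. The version 7.0 entry in the document history, used only as corroboration, explains the timing by reference to data collection and filter switch-on and does not mention allocation.

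**Effect on the estimate.** Let D be the between-arm difference in mean score at the end of March caused by allocation, and s the between-arm difference already present at a post-disclosure baseline. Write f = s/D.

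- March scores alone estimate D.
- A change score estimates D − s = (1 − f)D.
- Adjustment for the baseline score, with equal SDs and baseline-to-March correlation ρ, estimates D − ρs = (1 − ρf)D.

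The documents give neither f nor ρ. Both are assumed here, with ρ = 0.5:

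| f | Change score, share of D | Baseline-adjusted, share of D |
|---|---|---|
| 0 (completed before disclosure) | 100% | 100% |
| 0.10 | 90% | 95% |
| 0.25 | 75% | 87.5% |
| 0.50 | 50% | 75% |
| −0.25 (early shift of opposite sign) | 125% | 112.5% |

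A simulation with D = 0.40 SD, f = 0.25 and ρ = 0.5 gave 0.40 for March only, 0.30 for the change score and 0.35 for the adjusted model. The formulas give 0.40, 0.75 × 0.40 = 0.30 and 0.875 × 0.40 = 0.35.

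**The case against.** **Sections 6.4.4 and 6.4.5 may already settle the timing.** They do point to completion before randomisation. But the questionnaires are optional, the green light depends on aggregate home data, and nothing clearly holds randomisation until staff forms are returned. Section 6.17 addresses the timing of these forms specifically and allows a later date. At the least, the sections conflict.

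**Knowing the allocation may barely move the relevant items.** Outcome 2d concerns confidence in and use of IPC, whereas the item most open to influence is a belief about filters, and no scoring rule in the protocol places that item in 2d. The training described in 6.4.5 is practical, with no stated content on efficacy. Section 6.10 also excludes staff who consent residents. All of this stands, and it is why no size can be given.

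**The baseline still precedes exposure.** This stands if completion precedes switch-on: effects of living with running filters are then kept, and only the effect of knowing the allocation or of training is at risk.

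**Analysis detail belongs in the SAP.** This is accepted. Section 13.1.2 specifies neither a change score nor baseline adjustment for questionnaires. The outcome's definition as change over time, and the timing of its baseline, are nevertheless set in the protocol.

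Three stronger readings are tempting but not supported:

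- A reader might infer that the effect is certainly diluted. The sign of the early shift is unknown, and an opposite shift would inflate the difference.
- A reader might infer that this questionnaire is the measure by which relaxation of infection control will be judged. Section 6.17 gives that question to the process evaluation, which also uses interviews (Sections 8 and 8.3).
- A reader might extend the point to residents, whose baseline questionnaires follow consent and hence allocation. The protocol states no resident change-from-baseline outcome; resident outcome k is perception of the care home environment.

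**Conclusion.** The point holds as a minor one. Section 6.17 permits a staff baseline after disclosure of allocation and after device training, in conflict with what 6.4.4 and 6.4.5 imply. For outcome 2d, any allocation-related difference present at that baseline enters a change score one-for-one with reversed sign, and enters a baseline-adjusted estimate in proportion to ρ. Whether such a difference exists, how large it is and which way it runs cannot be determined from the documents; the percentages above are illustrations over an assumed range. The conclusion rests on some staff having answered after disclosure, which the protocol allows but does not show to have happened. The primary outcome and the sample size do not depend on these questionnaires.

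**What to change.** Reconcile Sections 6.4.4, 6.4.5 and 6.17 so that all three say staff questionnaires are completed before the home is told its allocation.

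For homes where this was not met, specify that:

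- only questionnaires completed before the home's disclosure date count as baseline; and
- otherwise, end-of-March scores are compared between arms, adjusted for the stratification factors with a random effect for home and without the post-allocation score, at least as a sensitivity analysis.

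The wording change costs little. The analysis rule loses some precision where no pre-disclosure questionnaire exists. It also needs a completion or receipt date for each form, and Section 6.10, which allows paper return by freepost, does not say that one is recorded. The current version is dated September 2024, after the planned end of the third winter, so rewording is unlikely to change when forms were completed. In practice the analysis rule will matter most.
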